## Abstract

**Background:**

According to the principles of Reablement, home care services are meant to be goal-oriented, holistic and person-centred taking into account the capabilities and opportunities of older adults. However, home care services traditionally focus on doing things *for* older adults rather than *with* them. To implement Reablement in practice, the ‘Stay Active at Home’ programme was developed. It is assumed that the programme leads to a reduction in sedentary behaviour in older adults and consequently more cost-effective outcomes in terms of their health and wellbeing. However, this has yet to be proven.

**Methods/ design:**

A two-group cluster randomised controlled trial with 12 months follow-up will be conducted. Ten nursing teams will be selected, pre-stratified on working area and randomised into an intervention group (‘Stay Active at Home’) or control group (no training). All nurses of the participating teams are eligible to participate in the study. Older adults and, if applicable, their domestic support workers (DSWs) will be allocated to the intervention or control group as well, based on the allocation of the nursing team. Older adults are eligible to participate, if they: 1) receive homecare services by the selected teams; and 2) are 65 years or older. Older adults will be excluded if they: 1) are terminally ill or bedbound; 2) have serious cognitive or psychological problems; or 3) are unable to communicate in Dutch. DSWs are eligible to participate if they provide services to clients who fulfil the eligibility criteria for older adults. The study consists of an effect evaluation (primary outcome: sedentary behaviour in older adults), an economic evaluation and a process evaluation. Data for the effect and economic evaluation will be collected at baseline and 6 and/or 12 months after baseline using performance-based and self-reported measures. In addition, data from client records will be extracted. A mixed-methods design will be applied for the process evaluation, collecting data of older adults and professionals throughout the study period.

**Discussion:**

This study will result in evidence about the effectiveness, cost-effectiveness and feasibility of the ‘Stay Active at Home’ programme.

**Trial registration:**

ClinicalTrials.gov: NCT03293303, registered on 20 September 2017.

## Background

Western countries with ageing populations, such as the Netherlands, have to deal with an increasing demand for health care, while financial resources and manpower are shrinking [1]. One strategy to face this challenge is to enable ‘ageing in place’, which is a common policy in these countries. Consequently, the proportion of older adults in Dutch long-term care facilities is decreasing and home care is becoming more important [2]. This is in line with the preference of most older adults, who want to stay at home for as long as possible, even if they suffer from fragile health and are faced with challenging social situations [3]. However, to enable ‘ageing in place’ it is important that older adults maintain their self-care capabilities.

Previous research has shown that physical activity can positively affect daily functioning of older adults [4–7]. Nevertheless, many community-dwelling older adults have a highly sedentary lifestyle [8]. In general, older adults spend approximately 80% of their awake time in sedentary activities which represents 8 to 12 h per day [9, 10]. Most research on stimulating physical activity of older adults, focuses directly on the behaviour of older adults, for instance by offering an exercise intervention, in group or individual format [7]. However, persuading older adults to become and continue to be physically active is a challenging task. Reasons for this may be a lack of motivation, fear (of falling), depression or a poor understanding of the long-term benefits of physical activity in older adults [11]. An alternative for these (classical) exercise programmes is to integrate physical activity in daily care, for example, in home care.

In the Netherlands, 20% of older adults use home care services [12]. Nurses and domestic support workers (DSWs) support them with personal care (e.g. washing and dressing) or domestic tasks (e.g. cleaning or doing the laundry), respectively. Unfortunately, they mainly provide support by taking over tasks instead of stimulating older adults to be active in physical and daily activities, as they are used to doing things *for* older adults rather than *with* them. This can result in a downward spiral, as they deprive older adults of their opportunities to engage in a routine range of movements necessary for maintaining underlying capabilities, resulting in further deconditioning and functional decline [13–15]. These negative consequences may be prevented by implementing Reablement in home care.

During the last decade, Reablement has been introduced in several countries (i.e. US, UK, New Zealand, Australia, Norway, and Sweden), but there is no internationally accepted definition of Reablement, and consequently a great variation between and even within countries exists in how Reablement is implemented [16, 17]. Nevertheless, Reablement initiatives have in common that day-to-day services are meant to be goal-oriented, holistic and person-centred taking into account the capabilities and opportunities of older adults instead of focusing on disease and dependency [18]. So far, evidence concerning the effectiveness and cost-effectiveness of Reablement is scarce and inconsistent [16, 17, 19–21]. A few studies have shown beneficial results with regard to physical activity [22], daily functioning [23–26], health-related quality of life [27, 28] or health care utilisation/ costs [23, 27–31]. Furthermore, little is known about how Reablement is implemented in practice and which client groups are more likely to benefit from Reablement than others [16]. Consequently, more research in the field of Reablement is needed.

In the Netherlands, recently, the ‘Stay Active at Home’ programme was developed based on international evidence and in close collaboration with Dutch and foreign stakeholders [18]. It is a training programme for home care professionals that aims to provide them with knowledge, self-efficacy, skills and social support to implement Reablement in practice. The feasibility of the programme and the research design have been evaluated in an exploratory trial (ClinicalTrials.gov: NCT02904889 (Smeets RGM, Kempen GIJM, Hansen WAG, Zijlstra GAR, van Rossum E, de Man-van Ginkel JM, et al. Experiences of home care professionals with the Stay Active at Home programme targeting reablement of community-living older adults. A qualitative study, submitted for publication)), which is part of the Basic Care Revisited project [32]. Semi-structured interviews that were conducted with home care professionals during the exploratory trial showed that professionals experienced the ‘Stay Active at Home’ programme as an empowering way to apply Reablement in home care (Smeets RGM, Kempen GIJM, Hansen WAG, Zijlstra GAR, van Rossum E, de Man-van Ginkel JM, et al. Experiences of home care professionals with the Stay Active at Home programme targeting reablement of community-living older adults. A qualitative study, submitted for publication). However, the effectiveness, cost-effectiveness and feasibility of the ‘Stay Active at Home’ programme are not yet known. Therefore, a two-group cluster randomised controlled trial will be conducted to evaluate whether its implementation leads towards a reduction in sedentary behaviour in older adults and thereby an increase in their level of physical activity. Furthermore, we will investigate whether the programme leads to more cost-effective outcomes in terms of older adults’ health and wellbeing. In addition, an extensive process evaluation will be conducted alongside the trial to provide information about 1) the implementation of the ‘Stay Active at Home’ programme; 2) its mechanisms of impact; and 3) contextual factors that may affect implementation and outcomes. This paper describes the study protocol of the cluster randomised controlled trial taking into account the SPIRIT 2013 Statement [33, 34].

## Methods/ design

### Objectives

This study evaluates the ‘Stay Active at Home’ programme. More specifically the aims are to get insight into the programme’s:Effectiveness with regard to sedentary behaviour of older adults (primary outcome). Furthermore, several secondary outcomes will be evaluated: physical activity, daily, physical and psychological functioning and falls *(effect evaluation)*.Cost-effectiveness from a societal perspective *(economic evaluation)*.Feasibility with regard to implementation, mechanisms of impact and contextual factors that may affect its implementation and outcomes *(process evaluation)*.

### Design

A two-group cluster randomised controlled trial will be conducted in the south of the Netherlands. Home care professionals (i.e. nurses and DSWs) in the intervention group will receive the ‘Stay Active at Home’ programme. Professionals in the control group will receive no additional training. Data for the effect and economic evaluation will be collected at client level by performance-based and self-reported measures. In addition, data from client records will be extracted. Data are assessed at baseline and 6 and/or 12 months after baseline. A mixed-methods design will be applied for the process evaluation at the client and professional level. Data will be collected throughout the whole study period. For practical reasons, the recruitment of older adults, the implementation of the programme and the data collection will be conducted in four phases. The recruitment of participants will be conducted between September 2017 and January 2018 (two teams, intervention group), November 2017 and January 2018 (two teams, control group), January and April 2018 (three teams, intervention group) and March and June 2018 (three teams, control group). The trial is registered at www.clinicaltrials.gov (#NCT03293303).

### Setting

This study will be conducted at MeanderGroep South-Limburg (www.meandergroep.com), a large healthcare provider that offers, among other services, different types of home care services in the region of South-Limburg: domestic services (e.g. cleaning and other household chores), personal care (e.g. assistance with bathing or dressing) and nursing services (e.g. wound care and injections). MeanderGroep has divided its region into 7 working areas, which are further subdivided into small-scale self-directed nursing teams, with on average 11 nursing teams per working area (range 3–28). Each team is guided by a district nurse (baccalaureate-educated registered nurse). The other team members are vocationally-trained registered nurses or certified nurse assistants. Domestic support is provided by DSWs, who work individually under supervision of a manager. They are linked to a working area, but not to a specific nursing team.

### Randomisation

For this study, ten nursing teams in five working areas (two teams per area) will be selected by the nursing team managers of MeanderGroep. To avoid contamination bias, managers will be asked to select two teams within each area that are not collaborating with each other. Furthermore, dementia teams will not be considered, as most of their clients potentially will not fulfil the inclusion criteria for older adults. The nursing teams will be pre-stratified with regard to their working area and randomised into either the intervention or control group within each working area. The clients and, if applicable, their DSWs will be allocated to the intervention or control group based on the allocation of the nursing team. The randomisation will be conducted by means of a computer-generated randomisation list. The researcher who will conduct the randomisation, will be blinded, will not be involved in this study and not familiar with the nursing teams. A flow diagram of the study design is shown in Fig. 1.

**Fig. 1 Fig1:**
[figure not shown]
Flow chart of the study

### Participants and recruitment

Two types of participants will be recruited for this study: older adults and home care professionals (i.e. nurses and DSWs).

#### Older adults

Several inclusion and exclusion criteria will be determined for older adults. Older adults are eligible to participate in this study if they: 1) receive homecare services by the selected teams; and 2) are 65 years or older. Older adults will be excluded if they: 1) are terminally ill or bedbound; 2) have serious cognitive or psychological problems; or 3) are unable to communicate in Dutch. The participating district nurses, who are leading the nursing teams and are familiar with all clients, will check clients on the eligibility criteria based on their clinical judgement. This will result in a list of eligible clients per team. Subsequently, the recruitment of older adults will start, which consists of three steps. First, older adults will receive a short information letter and flyer about the study on behalf of MeanderGroep. Second, older adults will receive a short telephone call to assess whether they are potentially interested in participating in this study. Third, a home visit will be conducted by the research team (author [name] or research assistant) to provide additional information. When older adults agree to participate, the baseline data will be assessed. Participation of older adults is voluntary; they are informed about the study and were asked for written informed consent. Older adults may withdraw from the study for any reason at any time.

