*Adaptations* Alterations made to the intervention	Researchers	IG	Project logbook	– if applicable: changes in content, procedures, activities and processes	Continuously throughout the implementation phase
*Reach* Extent to which the target group was reached	Professionals	IG	Project logbook	– Number of professionals who will refuse, drop out or complet the programme and reasons for refusal and drop-out	Continuously throughout the implementation phase
	Older adults	IG	Project logbook	– Number of older adults who will refuse, drop out or complete the programme and reasons for refusal and drop-out	Continuously throughout the implementation phase
Mechanisms of impact					
Mechanisms that are expected to produce change	Professionals	IG, CG	Self-report questionnaire	– Knowledge test and self-efficacy and outcome expectation questionnaire inspired by the work of Resnick et al. [75–77] – Additional evaluation questions (which cover the different topics of the programme)	6 and 12 months after baseline
	Older adults	IG, CG	Self-report questionnaire	– Self-efficacy and outcome expectation questionnaire inspired by the work of Resnick et al. [78]	6 and 12 months after baseline (with data for effect and economic evaluation)
Contextual factors					
Factors that may influence the implementation/ outcomes of the intervention	Professionals and other stakeholders (e.g. interventionists, managers)	IG	Semi-structured (group) interviews	– a.o. facilitators and barriers in applying ‘Stay Active at Home’ in practice	At the end of the implementation phase
	Researchers	IG	Project logbook	– a.o. facilitators and barriers in applying ‘Stay Active at Home’	Continuously throughout the implementation phase

*IG* intervention group, *CG* control group

^a^Need to be further specified

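### District nurses list eligible clients by clinical judgement, very probably after their team's allocation is set, so team-level randomisation does not protect which clients are listed and consent

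*Protocol article*

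**What the plan says.** Under Randomisation, "ten nursing teams in five working areas (two teams per area) will be selected by the nursing team managers of MeanderGroep", and one team per area goes to each arm. Clients are not randomised: they and their domestic support workers are assigned "based on the allocation of the nursing team". The only blinding mentioned is that of the person who draws the allocation: "The researcher who will conduct the randomisation, will be blinded, will not be involved in this study and not familiar with the nursing teams".

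Under Older adults, the district nurses who lead the teams "will check clients on the eligibility criteria based on their clinical judgement", which yields a list per team. One exclusion is that clients "have serious cognitive or psychological problems"; the article gives no instrument or threshold for it. Recruitment from the list follows by a letter sent for the care provider, a telephone call and a home visit by the research team. The Discussion confirms that the research team obtains consent, and that recruitment by nurses was a feature of the exploratory trial that has been changed.

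Under Design, the windows are set by arm: "between September 2017 and January 2018 (two teams, intervention group), November 2017 and January 2018 (two teams, control group"), then January to April 2018 for three intervention teams and March to June 2018 for three control teams.

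The Reach row of Table 3 covers "Number of older adults who will refuse, drop out or complete the programme and reasons for refusal and drop-out", for the intervention group only.

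**The concern.** When clusters are randomised first and individuals enter afterwards, the arms are comparable at client level only if entry does not depend on the arm. Here entry begins with a judgement by the leader of the team. A nurse who expects to be trained could, without intending it, list clients who seem able to respond, or apply the cognitive and psychological exclusion more strictly or more loosely than a control colleague. Consent could also differ if those who telephone and visit know the arm.

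The treatment effect is the intervention-by-time term. A stable difference in level between the client samples is largely absorbed by the baseline measurement. A difference in expected change is not, and would look like a programme effect or hide one. The Discussion names two limitations, and this is not one of them.

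**Working it through.** The article gives no figure on this point, so the check is the order of steps.

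1. **Is allocation fixed before recruitment?** The windows carry arm labels for all ten teams (2 + 2 + 3 + 3 = 10). Planning windows by arm requires the allocation to be known to the planners. The article does not say when the district nurses are told.

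2. **Does listing precede recruitment?** Yes. The list comes first, then letter, call and visit. No list drawn up before randomisation and no allocation-blind listing is described.

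3. **How much discretion is there?** Age, receipt of care, being bedbound and language are largely factual. The cognitive and psychological criterion is the main discretionary one.

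4. **How do the windows compare?** Counting calendar months:

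| Wave | Intervention | Control | Overlap |
|---|---|---|---|
| First (4 teams) | Sep–Jan, 5 months | Nov–Jan, 3 months | Nov–Jan |
| Second (6 teams) | Jan–Apr, 4 months | Mar–Jun, 4 months | Mar–Apr |

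Control teams open two months later in both waves. The lengths differ only in the first, and Trial status dates the first client enrolment to October 2017, so the contrast there may be nearer 4 against 3 months. Follow-up at 12 months returns each client to about the same season. The stagger therefore matters mainly for calendar time and the mix of new and existing clients.

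5. **What does the model adjust for?** Baseline outcome (as a repeated measure), baseline GARS, client type and working area. Tables 1 to 3 contain no cognitive measure. The PHQ-9 is collected but is not a listed covariate. The traits that the nurse judges are thus only partly covered.

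6. **How large could the bias be?** The document does not allow an estimate. For scale only, the target effect is 0.15 × 535.9 = 80.4 min/day, and 80.4 / 145.7 = 0.55 reproduces the stated effect size. Assume that a share *f* of one arm differs by *k* SD through selective listing. Ignoring baseline adjustment, the bias is *f* × *k* × 145.7:

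- *f* = 0.1, *k* = 0.25: 3.6 min/day, 5% of target
- *f* = 0.2, *k* = 0.5: 14.6 min/day, 18%
- *f* = 0.3, *k* = 1.0: 43.7 min/day, 54%

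Both *f* and *k* are assumptions. The SD describes the level of sedentary time, not its change, and no SD of change is given. The range shows only that the effect could be trivial or material.

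**The case against.** The strongest reply is that the nurses' knowledge of allocation is nowhere stated. The arm labels describe recruitment windows, and the article was written after recruitment began, so they may show only what its authors knew by then. Lists could have been made before disclosure, and the flow chart that might settle this is not shown. That stands: knowledge of allocation is a strong inference and should be called one.

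A reader might go further in four ways that the document does not support:

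- **That the nurses recruit.** They only list; the provider's letter and the research team recruit. This limits the nurses' influence but does not undo selective listing, and no blinding of the research team is stated.
- **That randomisation fails to protect the comparison.** Teams are randomised within area by an uninvolved researcher, and that protection stands.
- **That refusals in the control group go unrecorded.** The Reach row is a process measure of the programme, so its restriction to the intervention group is natural, and its content is footnoted as still to be specified. It shows only that this log, as written, cannot compare the arms.
- **That the windows are unequal throughout.** In the second wave, with six of the ten teams, they are equal in length.

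The covariate adjustment also deserves credit. It lowers the risk from measured differences but cannot reach unmeasured ones.

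**Conclusion.** The point holds as a risk of identification bias within teams. Listing by clinical judgement, by the leaders of teams whose recruitment windows are set by arm and with no concealment described, lets client selection differ by arm. The planned adjustment reduces this without removing it. The conclusion rests on the inference that allocation is known when lists are made; if lists were closed before disclosure, the concern about listing falls away and only that about consent remains.

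No size can be attached. Any stated percentage of the target effect would be an assumption restated, and the document does not show that selection has in fact differed. The matter merits correction because it touches the primary comparison and the remedy is cheap, not because bias has been demonstrated.

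**What to change.** 1. For any team whose district nurse has not yet been told the allocation, obtain a dated list of all clients aged 65 or over, with the eligibility decision and reason, before disclosure, and recruit from it.
2. Record clients who enter care later separately, since client type is a planned covariate and new clients should not be lost. Run a sensitivity analysis restricted to the pre-disclosure list.
3. In all teams and both arms, log the numbers listed, excluded with reason, approached, refusing and dropping out, and report them by arm and team. Extending the Reach row of Table 3 to the control group would serve.
4. Align the windows of the two teams in an area where practicable.
5. Where allocation is already known, which may be all ten teams since recruitment has begun, state possible identification bias as a limitation. Item 3 remains worthwhile in that case.

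The cost is slightly more logging and some re-sequencing. Clients who enter care after the list date fall outside the protected list, so the sensitivity analysis will be smaller and will contain few new clients.

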#### Home care professionals

All nurses of the participating nursing teams are eligible to participate in the study. There will be no specific inclusion and exclusion criteria for them. DSWs are eligible to participate if they provide services to clients who fulfil the eligibility criteria for older adults. DSWs will be traced via their managers, who receive the list of eligible older adults from the research team (author [name]). Based on this list, the manager will inform the research team if clients also receive domestic support of MeanderGroep and by whom. Consequently, these DSWs will be invited to participate in the study.

